### Human Participants

#### Study Population

Focus groups and structured interviews will be conducted for all aims. Qualitative methods will include adult patients with SCI/D and seating and mobility therapy specialists. Adults with a SCI/D will be the participants for aims 2 and 3. As needed, we will capture additional input from other stakeholders involved in the proposed implementation process to ensure that we are gathering views from a broad range of affected individuals as per the CFIR framework. These individuals may include therapy managers, IT staff, data security staff, scheduling staff, and industry representatives.

#### Recruitment

Following IRB guidelines, manual and power wheelchair users with traumatic or atraumatic SCI/Ds will be enrolled for the study. The inclusion and exclusion criteria were chosen to include wheelchair users with SCI/D who are at risk for pressure injury development. Recruitment will be purposeful in achieving the desired equal distribution of power and manual wheelchair users and individuals with paraplegia and tetraplegia. For study randomization in aim 3, we will use a stratified, blocked randomization method to ensure even distribution of important predictor and confounding variables in the intervention and control groups. Announcements for participation in this study will be made by personnel directly to patients through mailed letters, phone calls, and word of mouth. Upon determining a person’s eligibility, an appointment (via phone or in person) will be made with the study coordinator to explain the research project, confirm eligibility, and collect the necessary demographic data.

#### Inclusion and Exclusion Criteria

We will enroll adult men and women, aged between 18 and 80 years, with SCI/D at C4 or below, who have a lack or absence of sensation, are primary wheelchair users, and are at high risk for pressure injury. For aims 2 and 3, participants must have had a seating clinic visit or be scheduled for a seating clinic visit. Participants must demonstrate the ability to independently access the AW-Shift system app on a mobile phone or tablet and be able to participate in web-based visits or meetings with the research team. Participants will be excluded if they are unable to consent, have an active stage-4 wound at the seating surface site, do not have adequate resources or support for use of the AW-Shift technology in their home environment, or are currently receiving palliative care. We will enroll current occupational or physical therapy staff for aim-1 qualitative and survey feedback.

#### Potential Risks

There is the potential for skin irritation from sitting on a pressure mat for long periods. Participants may sit on the pressure mat throughout the day or may simply use it for short periods while performing their prescribed activities. Participants will be instructed to do a skin check every day and log their findings.

Participants are instructed to call the study coordinator if a new area of skin breakdown or wound occurs while they are using the pressure mat or if a current wound worsens. The participant will be asked to remove the mat until the skin breakdown or wound resolves. If the area does not resolve and worsens further, the participant will again contact the study coordinator and will then be referred to their typical clinical care provider in the case of a potential, new-onset incidence of pressure ulcers of stage 3 or 4. Initializing and deploying the AW-Shift system will require performing transfers and weight shifts. Transfers always have some risk of injury or fall, and the participant will be advised to transfer in their usual manner. Weight shifts will include typical functional movements, such as leaning forward and sideways, but participants will be instructed to only perform weight shifts with which they are comfortable. Risks from transferring on their own while the sensors are on the wheelchair are no different than transferring without the sensors present.

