#### Home and Community Use of the AW-Shift System

Participants will use the system for an estimated 2 weeks before their clinical visit. Participants will have easy access via phone; secure, web-based format; email; and SMS text message for technical and therapy support. A potential prescription could include (but not be limited to) mapping the variety of surfaces the participant sits on in the home and community (the system can be used on any surface), completion of daily weight shift protocols to assess participant positioning on their cushion, measurement of how the participant performs weight shifts with and without reminders provided by AW-Shift, and measurement of the effectiveness of the weight shifts to offload pressure.

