#### Study Design

This single-site randomized controlled trial will use a modified intention-to-treat analysis. Randomization will be a stratified, block randomization with stratification based on wheelchair type (manual vs power) and current wound severity (no wound or stage 1 vs stage 2 or stage 3). The intervention group (26/52, 50%) will receive the connected care model that used AW-Shift in combination with telehealth. The control group (26/52, 50%) will receive the standard of care that uses telehealth when appropriate. The statistician will be masked to the group allocation information for the outcome measure analysis.

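### During mat use, the only required clinical referral for skin breakdown waits for a non-resolving, worsening, potential new-onset stage 3 or 4 ulcer, so an open stage 2 wound has none before the scheduled visit

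*Protocol article*

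**What the plan says.** Potential Risks, in the protocol article, gives the rule in four steps.

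- Self-monitoring: "Participants will be instructed to do a skin check every day and log their findings".
- First report: for a new area of breakdown, or a current wound that gets worse, the participant calls the study coordinator and is asked to take the mat away until the area resolves. No clinical assessment is attached to this call.
- Second report: "If the area does not resolve and worsens further, the participant will again contact the study coordinator".
- Referral: the participant is then "referred to their typical clinical care provider in the case of a potential, new-onset incidence of pressure ulcers of stage 3 or 4".

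The population and exposure are set elsewhere. Inclusion and Exclusion Criteria enrols people "who have a lack or absence of sensation, are primary wheelchair users, and are at high risk for pressure injury". The only wound-related exclusion is for those who "have an active stage-4 wound at the seating surface site". Study Design (aim 3) stratifies on "current wound severity (no wound or stage 1 vs stage 2 or stage 3", so stage 2 and stage 3 wounds are expected at entry. Home and Community Use of the AW-Shift System states: "Participants will use the system for an estimated 2 weeks before their clinical visit".

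**The concern.** The text joins three conditions before a clinician must be involved: no resolution, further worsening, and a potential new-onset ulcer at the two most severe stages. Two problems follow.

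First, the threshold is high. A coordinator who follows the text and hears of an open stage 2 wound asks for the mat to be removed and has no instruction to refer. A wound that stays as it is, neither healing nor worsening, never reaches the second step.

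Second, *new-onset* fits poorly with a trial that admits stage 2 and 3 wounds. If such a wound worsens, the first step plainly applies, but two coordinators could decide differently on whether the referral step does.

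Participant safety is at stake: a known wound could wait up to about 2 weeks for a required clinical look, in people chosen for high risk of recurrence.

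**Working it through.** **Reading the rule against each case**

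| Reported during mat use | First step | Referral required by the text? |
|---|---|---|
| New stage 1 area, resolves | Call, mat removed | No (reasonable) |
| New stage 1 area, persists | Call, mat removed | No |
| New open stage 2 wound | Call, mat removed | No |
| New wound, persists without worsening | Call, mat removed | No |
| New wound, worsens to possible stage 3 or 4 | Call, mat removed, second call | Yes |
| Entry stage 2 wound worsens to possible stage 3, or stage 3 to 4 | Call, mat removed, second call | Unclear; can be read as yes |
| Entry wound worsens within its stage | Call, mat removed, second call | Unclear; more naturally no |

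**Does any other section require earlier referral?**

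- Skin Safety (aim 2): skin is tracked and device use stops at signs of trouble. No referral.
- Home and Community Use: "Participants will have easy access via phone; secure, web-based format; email; and SMS text message for technical and therapy support". This is on request.
- Telehealth Clinical Visit and Study Procedures: after the 2 weeks of use a therapist sees the participant online, asks for confirmation of a same-day skin check and decides the next steps in care. This is a planned contact, but it comes at the end of the exposure.
- Initiating and Conducting the Pilot Clinical Trial: urgent matters reach the principal investigator within 18 hours and are reported to the IRB. This is a reporting line, not a referral.

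None requires an earlier referral. The removal-of-device statement in Skin Safety does not conflict with Potential Risks.

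**Size of the exposure (aim 3)**

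The document gives no figure for this, so there is none to reproduce. Inputs: 26 intervention participants (Study Design) and 14 days of use (Study Procedures), taken as one full period per person.

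- Participant-days: 26 × 14 = 364. Person-years: 364 / 365 = 0.997.
- With a constant annual rate r, expected new wounds = 0.997 × r, and P(at least one) = 1 − exp(−0.997 × r).

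The rates come from the eligibility questions in Study Population (aim 3), read as annual rates. This reading is an assumption.

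| Rate per year | Expected new wounds | P(at least one) |
|---|---|---|
| 0.5 (one every couple of years) | 0.50 | 39% |
| 1.0 (at least one a year) | 1.00 | 63% |
| 2.0 (assumed for the most severe group) | 1.99 | 86% |

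As a cross-check, treat the Background percentages as annual risks p, which the article does not say they are. Then q = 1 − (1 − p)^(14/365), expected = 26q and P(at least one) = 1 − (1 − q)^26. For p = 25%, 38% and 80%, the expected numbers are 0.29, 0.47 and 1.56, with chances of 25%, 38% and 80%.

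These figures count new wounds of any stage and cause. They do not measure harm from late referral, which the article gives no means to estimate. Worsening of entry wounds comes on top and cannot be estimated either.

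**The case against.** **Detection is early and the device comes off at once.** This stands. Any new or worsening area triggers a call, and the mat is removed at the first report. The gap concerns what happens next.

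**A therapist visit is already scheduled.** This stands and caps the gap at roughly the 2 weeks of use. It does not help a wound reported on day 2 or 3.

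**The population's lost sensation adds nothing.** A reader might infer that the rule is late because participants cannot feel a wound. Sensation bears mainly on noticing a wound, and the daily check deals with that. The point does not rest on sensation.

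**Progression of an entry wound can count as new-onset.** This is fair for stage 2 becoming 3 or 3 becoming 4, and the word *potential* means that staging need not be confirmed. A reader might infer that entry wounds are excluded from referral. The text supports only ambiguity, clearest for worsening within a stage.

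**The referral clause could mean as a precaution against stage 3 or 4.** On that reading any further worsening leads to referral and the new-onset problem softens. Non-resolution and further worsening are still required first, so the open or static stage 2 wound remains uncovered.

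**The text is provisional and operating procedures will follow.** IRB approval for aims 2 and 3 is still to be sought, and changes are expected. That makes correction easy. It does not make this a condensed detail, because the article states the threshold outright.

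**Nothing suspends usual care, and what counts as late is a clinical judgement.** Both are true. Participants may seek care themselves, and the document sets no standard for when stage 2 needs referral. This limits the weight of the point but does not remove it.

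**Conclusion.** The rule as written sets the required referral too far along. During about 2 weeks of mat use, an open stage 2 wound, or one that persists without worsening, has no required clinical referral until the scheduled therapist visit. Whether worsening of an entry stage 2 or 3 wound triggers referral is ambiguous. Early detection, mat removal, support on request and the visit limit the gap without closing it.

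The numbers are small: about 0.5 to 1.0 new wounds expected in aim 3 on the eligibility-question rates, up to 2.0 on the assumed highest rate. This rests on full 14-day use, constant rates and self-description read as incidence.

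Two stronger readings should be resisted. A reader might take these counts as expected harm; they are not. A reader might also infer bias in the primary outcomes. The document does not support that: mat use precedes the 365-day abstraction window, which starts after the study visit. This is a cheap safety improvement, not a threat to the trial's results.

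**What to change.** Keep mat removal at the first call and replace the referral sentence in Potential Risks with a graded rule, for example: *Any open wound (stage 2 or higher) and any worsening of a wound present at enrolment is referred to the participant's usual care provider when first reported. Any new stage 1 area is referred if it does not resolve within a short interval after mat removal, set by the clinical team.* An interval of 24 to 48 hours would be one choice; it is an assumption, not taken from the document.

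The change costs one sentence and one coordinator step, and can be made before IRB approval for aims 2 and 3 is sought. The extra referrals in aim 3 would be few:

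- New wounds: at most about 0.3 to 2.0, from the ranges above. This is an upper bound, since some would be stage 1 or already referred under the present rule.
- Persistent stage 1 areas: if 1% to 5% of 364 daily checks show a new red area (3.6 to 18.2 calls) and 10% to 30% of those persist, 0.4 to 5.5 referrals. Both percentages are assumed.
- Worsening entry wounds: additional, not estimable.

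Some referrals will prove unnecessary. Mat-period wounds will also be charted somewhat more fully in the intervention arm only, so a wound lasting past the visit could carry an earlier date or stage there. To contain this, leave the 365-day window and the chart as outcome source unchanged, and class wounds first charted before the study visit as prevalent in the primary effectiveness analysis, by the same rule in both arms.

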### Focus Group Guide

Questions were created for the clinicians’ structured interviews and focus groups. A sample of the question list is shown in Textbox 1.

Sample of question list.What are some of the challenges you come up against when teaching a patient with spinal cord injuries and related disorders (SCI/D) about pressure relief?On the basis of feedback from our patients of how very useful real-time information is to their pressure relieving behavior. What do you think about the having the real-time image available all the time to the patient?Do you think having that image available will assist you in monitoring and teaching seating behavior?What other information, or data, would you want to be readily available to you to monitor the patients’ learning of pressure injury prevention behaviors?For example, would it help you to know how many pressure reliefs the patient conducted during the previous hour?Would you like the data available for you to be in a particular format?For example, an average number of pressure reliefs conducted over the past four hours, or the percentage of offload over a certain period?How far back would you want data available for monitoring or educating pressure relieving behaviors?Do you want the information pushed to you?Can you think of any data that would not be helpful for you to be able to access?For example, when reviewing the patients pressure relieving behavior would you find it useful to know the actual peak psi’s that occurred over the previous period of monitoring, or would that be too much information?

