#### Patient and Clinician Needs Assessment

Overall, 2 focus groups, 1 for adults with SCI/D and 1 for clinicians from the Seating Clinic and Wound Care, will be conducted to determine the needs and priorities of each group for improving the assessment of seating and mobility needs. A focus group guide, drawn from CFIR’s Interview Guide Tool [30], will be used for each group to better understand how expanded seating pressure information captured during the daily life of patients could better inform seating and mobility therapy visits. The discussion will include brainstorming of types of information that would be of value and identifying barriers to and facilitators of attaining the information. There will be an emphasis on understanding the concerns about the complexities of a new process as it relates to the outer setting, inner setting, and individual characteristic constructs of the CFIR model [31]. The focus groups will be conducted through a Health Insurance Portability and Accountability Act–compliant web-based meeting format (Zoom; Zoom Video Communications). The discussion will be recorded for analysis.

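### One clinician question about the always-available real-time image, with its follow-up, is leading and may inflate favourable answers about that feature

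*Protocol article*

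**What the plan says.** The Focus Group Guide section states that questions were written for the clinicians' "structured interviews and focus groups. A sample of the question list is shown in Textbox 1". The printed list opens with "What are some of the challenges you come up against when teaching a patient" about pressure relief. The second item begins "On the basis of feedback from our patients of how very useful real-time information is to their pressure relieving behavior" and goes on to ask "What do you think about the having the real-time image available all the time to the patient". The third asks "Do you think having that image available will assist you in monitoring and teaching seating behavior". The remaining items concern which data clinicians want, in what format, how far back and how delivered. The list ends with "Can you think of any data that would not be helpful for you to be able to access" and an example of such data.

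The Patient and Clinician Needs Assessment section describes one focus group for adults with SCI/D and one for clinicians. It says that both barriers and facilitators will be discussed, and adds: "There will be an emphasis on understanding the concerns about the complexities of a new process". The Draft Plan and Follow-up Focus Group section says that the needs assessment refines the draft implementation plan.

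**The concern.** A needs assessment should record what clinicians think before they learn which answer the investigators or their patients favour. The second item reverses that order: the respondent hears that patients already rate the information highly and is then asked for an opinion. A clinician with reservations would have to disagree with reported patient experience to voice them. The third item can be answered yes or no, and only the benefit is named.

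What is at stake is the credibility of clinicians' apparent support for the live image. The Results section says that aim-1 findings are to be published. The Expected Outcome section of the Discussion already states, from earlier projects, that therapists strongly want a visual system. Approval gathered with a primed question adds little independent support for that belief.

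**Working it through.** No formula applies, and the plan gives no figure to reproduce. The check is a reading of the printed questions, set against the stated purpose of aim 1.

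**1. Count and classify the sample list.** Counting those introduced as examples, there are 11 questions:

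| Questions | Subject | Framing |
|---|---|---|
| 1 | Challenges in teaching pressure relief | Neutral, problem first; not about the system |
| 2 | Live image always available to the patient | Open question, preceded by a favourable verdict |
| 3 | Whether the image helps the clinician | Closed; benefit only |
| 4 to 9 | Other data wanted, format, look-back, delivery | No stated verdict |
| 10 and 11 | Data that would not help, with an example | Invites a negative answer, about data items |

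The rows add up: 1 + 1 + 1 + 6 + 2 = 11.

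**2. Locate the leading wording.** Only question 2 states a verdict. Question 3 repeats no verdict, but it follows directly on the same subject and offers only the positive side. The affected part is therefore one item and its follow-up.

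**3. Look for a counterweight on the same feature.** Questions 10 and 11 invite criticism, but of data items such as peak pressures. Question 1 asks about difficulties, but in teaching patients. No question shown asks what could go wrong with a live image. Question 11 asks whether the information would be useful or too much, so the list itself contains a two-sided question. Questions 2 and 3 do not follow that pattern.

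**4. Compare with the stated purpose.** The needs assessment is to cover barriers and to emphasise concerns. The two image questions, as printed, do not serve that purpose for the image.

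**5. Trace where the answers go.** Coding begins from a template built on the guide topics (Qualitative Outcome Measures and Data Analysis), and the needs assessment refines the draft plan. The plan then passes through further focus groups, aim-2 testing and consensus before aim 3.

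**6. Check what can still be changed.** The therapist focus group is planned at n=10 (aim-1 Sample Size), and 6 participants had been recruited to the clinician arm at submission (Results). If that target holds, 10 − 6 = 4 clinicians were still to be recruited. Two to three iterations of focus groups and refinement are expected. The article does not say how many sessions had already been held.

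**The case against.** The strongest reply is that an excerpt cannot convict a whole guide. The article says plainly that "A sample of the question list is shown in Textbox 1". The full guide is drawn from an established implementation interview tool, and barriers and concerns are planned content. That stands: the count of 11 describes the sample, not the instrument. It does not make the printed item neutral.

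The follow-up can also be defended as an ordinary yes/no question. That is fair in isolation, but here it comes straight after the verdict and no question about drawbacks accompanies it.

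A reader might go further and infer that the needs assessment as a whole is steered toward approval, and with it the aim-3 intervention. The document does not support this:

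- The list opens with challenges, and a separate patient group is planned. The printed guide is for clinicians only, and the article does not say which aim-1 round uses it.
- The questions that bear most on the mHealth report (which data, what format, what look-back, what is unhelpful) carry no approving lead-in. The live image is an existing feature of the system and is distinct from that summary report.
- In aim 2 the plan is tested and adjusted, therapists complete surveys and interviews after using it, and case summaries go back to the focus groups, with consensus on any open points before aim 3.
- The primary aim-3 effectiveness outcomes are abstracted from medical records, so the wording of an aim-1 question does not bias the comparison between arms.

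Two further inferences also fail. The article does not say who moderates the sessions, so it cannot be said that the system's developers run them. That suppressed objections would later appear as low adherence in the pilot is conjecture.

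**Conclusion.** The point holds in a narrow form. One printed clinician item states a favourable verdict before asking for an opinion, its follow-up names only a benefit, and nothing shown asks about drawbacks of the same feature. Favourable answers about the always-available image may be inflated as a result.

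The point is minor. The size of any inflation cannot be estimated from the document, and the conclusion reaches no further than this one feature. It assumes that the questions are put as printed and that no unprinted item supplies the missing prompt on drawbacks. If one does, the imbalance shrinks, but the lead-in should still go.

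**What to change.** Delete the sentence reporting patient feedback. Describe the feature in neutral terms and ask how, if at all, a live pressure image available to the patient would change the clinician's work. Reword the follow-up to ask what effect, if any, the image would have on monitoring and teaching. Add a matching prompt on problems or drawbacks the clinician would expect.

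Use the new wording in any remaining sessions. Mark in the coding which transcripts used the old wording, so that favourable remarks about the image in those transcripts are read with the lead-in in mind and can be compared with later ones.

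The work is two reworded questions and one added prompt in a qualitative study approved as exempt, with at most a minor notice to the review board. The downside is that wording differs slightly between early and late sessions. If all sessions have already been held, only the marking of transcripts and a sentence of caution in the aim-1 report remain possible.
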